## Methods

### Study design

We use a pilot, randomized, sham-controlled, double-blind clinical study design. Twenty patients are being randomly assigned to PMC tDCS plus CIMT or sham tDCS plus CIMT groups. All outcomes are collected at pretest and at post-test after 5 weeks of intervention. At 3-month follow up, outcomes of hand function are collected to examine retention.

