**Figure 2 F2:**
[figure not shown]
**Power analysis: power was determined by simulation.** Lower and upper lines define exactly the 95% CI for power, calculated based on the binomial distribution. N is the total sample size. The analysis was performed at a 0.05 significance level considering 2 × 2 factorial analysis of variance (ANOVA) (tDCS plus CIMT and sham tDCS plus CIMT from pretest to post-test). Power has been estimated here for an interaction term (A *C).

Although the estimated sample size appears small, it is commensurate with the pilot exploratory nature of our study. Pilot studies involving brain stimulation generally use smaller sample sizes compared to rehabilitation trials
[28] because contraindications to brain stimulation/imaging are constraining. Still, we anticipate having adequate statistical power based on prior evidence where despite enrolling a total of 14 to 30 subjects, several studies report significant benefit of adjunctive stimulation
[8,30,44]. Additionally, use of a repeated-measures design further provides greater power. Studying neural mechanisms with fMRI and tractography in limited sample sizes is challenging. Given the exploratory nature of our pilot study, we would be able to highlight elemental neural mechanisms of recovery. Previously, in a three-group, randomized controlled study design with a small sample of 20, we deciphered correlates of fMRI
[37]. Recently too, Stagg *et al*.
[64] show differences in fMRI activation across varying types of tDCS interventions in 11 patients with stroke. Without overemphasizing the importance of small pilot studies, we stress instead the significance of large-scale studies in generating clear evidence of efficacy. Our current pilot exploratory study is a step in that direction as it would offer estimates of effect size related to PMC tDCS and neural markers that can serve as entry criteria.

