To assess neural substrates of recovery, both groups will be compared for change in inter-hemispheric balance (fMRI), fc and transcallosal inhibition and corticospinal conduction (TMS) from pretest to post-test. To understand whether effects of interventions vary across patients and factors explaining such variance, an ideal method would have involved identifying clinical, pathologic and neural factors that would predict the change in UEFM. However, since the statistical power of the study may be inadequate to pursue this analysis, we will follow an alternative method. Patients who achieve ≥3.5 gain in the UEFM score (criterion of clinical improvement defined in a previous clinical trial of invasive cortical stimulation)
[8] after 5 weeks of the intervention would be called responders. We will investigate whether the proportion of responders versus nonresponders includes a greater majority of patients from the tDCS group (Chi-square analysis). More importantly, we will compare clinical, pathologic and neural indicators between responders and nonresponders (independent samples *t*-test). These will include: baseline UEFM, location of disease (Oxford Stroke classification: total anterior circulation or partial anterior circulation or lacunar strokes)
[66], residual function and integrity of corticospinal tracts on the stroke-affected side measured with TMS and diffusion tensor imaging respectively.

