[69]. If we find that responsive patients show distinctive characteristics, such as patent and functioning white matter tracts et cetera, then these would serve as entry criteria for the future. Unfortunately it may also mean that stimulation may be more fruitful only for a limited few, but this information would optimize resource allocation. For patients showing limited to no response, we would identify whether functioning of alternate areas (as identified on fMRI) and patency of tracts from other regions (from tractography) may hold greater meaning. A patient-guided approach to utilizing such residual resources will then be created, employing alternate rehabilitation methods and/or stimulating patient-specific loci.

Knowing mechanisms of long-term pairing can help address why chronic effects are not as robust. Even though singular sessions or short-term paradigms show benefit
[11,13,16,22,29,30], trials incorporating long-term training have failed to witness an advantage
[15-19]. Divergent success across short- and long-term studies may also be an effect of dosage. Stimulation may have an initial accelerative effect
[25,32] manifested in the short term, but over the long term, the effect of rehabilitation itself may become robust
[37,70], diminishing the comparative effect size.
[15-19]. Confounding from individual variance may also factor in; if stimulation in rehabilitation were truly effective, its differences from rehabilitation would evolve over time; on the flip side, if all gains were solely related to variance across individuals, then a long-term study would show no difference, and short-term studies would be easily confounded. Short-term designs also have the added advantage of higher treatment fidelity; standardized laboratory-based paradigms can be delivered in short-term approaches more easily
[13,14,22,29,45], whereas longer protocols of clinical rehabilitation suffer from variance in treatment delivery
[8-10,16,17,23-25,30,44]. However, exploring stimulation delivered with long-duration rehabilitation still carries greater clinical utility, despite challenges to adherence and fidelity, because short-term paradigms, though invariably positive, do not correlate with long-term outcomes
[13,14,22,23,29-31,45].

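### Markers are said to become entry criteria for later trials, but the planned t-test of means gives no cut-off and no classification error rate

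*Protocol article*

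**What the plan says.** Statistical and data analyses defines responders by the change in the upper extremity Fugl-Meyer (UEFM) score over the 5 weeks of intervention: "Patients who achieve ≥3.5 gain in the UEFM score" are responders. The definition makes no distinction between the two arms. The section regards prediction of UEFM change from clinical, pathologic and neural factors as the ideal approach but does not adopt it: "since the statistical power of the study may be inadequate to pursue this analysis, we will follow an alternative method". The substitute is a comparison of the two outcome groups: "More importantly, we will compare clinical, pathologic and neural indicators between responders and nonresponders", by independent-samples t-test. The indicators listed are baseline UEFM, lesion location by Oxford class, and the function (TMS) and integrity (diffusion tensor imaging) of the corticospinal tracts on the affected side.

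The use to be made of the result appears in two other places. Sample size estimation, in the text after Figure 2, says the study would offer "neural markers that can serve as entry criteria". The Discussion says that if responsive patients show distinctive characteristics, "then these would serve as entry criteria for the future". The article describes no cut-off, sensitivity, specificity or validation step between the comparison and that use.

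**The concern.** The t-test asks whether two group means differ. An entry criterion asks on which side of a line a single patient falls, and how often that answer is wrong. In a sample of 20, a significant difference in means is compatible with heavy overlap between the groups. So the step from a marker that differs between the groups to a marker that serves as an entry criterion is not supported by the stated analysis, even if the difference is real and only one marker was tested.

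This is more than a detail left to an analysis plan, because the article states both the test and the conclusion to be drawn from it. At stake is the use made of the second objective. A later trial that adopted such a criterion could exclude many patients who would have improved and admit many who would not. The primary UEFM comparison in this trial is unaffected.

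**Working it through.** The protocol gives no classification figure to reproduce. The check asks how well an indicator separates the groups when it only just passes the planned test.

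**Inputs**
- Total sample 20 (Study design): "Twenty patients are being randomly assigned to PMC tDCS plus CIMT or sham tDCS plus CIMT groups".
- Test: independent-samples t-test (Statistical and data analyses).
- Significance level: two-sided 0.05, an assumption. The protocol gives 0.05 only for the power analysis (Figure 2 legend): "The analysis was performed at a 0.05 significance level".
- Split into responders and nonresponders: not given. 10/10 is assumed first, then varied.
- Further assumptions: a continuous, normal indicator, equal SDs, and a true difference equal to the observed one.

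**Smallest significant difference, 10/10**
- The critical t on 18 df is 2.101.
- d = 2.101 × √(1/10 + 1/10) = 2.101 × 0.447 = 0.94 SD.

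**Separation**
- AUC = Φ(d/√2) = Φ(0.664) = 0.75.
- The Hanley-McNeil standard error is 0.112, so the 95% CI is 0.747 ± 1.96 × 0.112, or about 0.53 to 0.97.

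**Errors at a midpoint cut-off**
- Responders turned away = nonresponders admitted = Φ(−d/2) = Φ(−0.47) = 31.9%.

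**Other splits and sample sizes, midpoint cut-off**

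| Responders/nonresponders | d | AUC | Error on each side |
|---|---|---|---|
| 10/10 | 0.94 | 0.75 | 31.9% |
| 14/6 | 1.03 | 0.77 | 30.4% |
| 17/3 or 3/17 | 1.32 | 0.82 | 25.5% |
| 8/8 (16 evaluable) | 1.07 | 0.78 | 29.6% |

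At N = 20, with at least 3 patients in each group, the error on each side runs from 25.5% to 31.9%.

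**Other cut-offs, 10/10, d = 0.94**
- Responder loss held to 10%: nonresponders admitted = Φ(1.282 − 0.94) = Φ(0.342) = 63%.
- Nonresponder admission held to 20%: responders lost = Φ(0.842 − 0.94) = Φ(−0.098) = 46%.
- Nonresponder admission held to 10%: responders lost = 63%, by symmetry with the first line.

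**If the true difference is smaller than the observed one**
- At a true d of 0.5, the midpoint error is Φ(−0.25) = 40%. At a true d of 0 it is 50%. Simulation with the cut-off set at the sample midpoint gave the same values, about 40% and 50%.

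**Stronger evidence, 10/10**
- At p = 0.01, d = 1.29, AUC = 0.82, and the midpoint error is still 26% on each side.

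**The case against.** The best defence is that the article is modest about this work. It calls the study a pilot and exploratory, admits that power may be too low for a prediction analysis, makes the Discussion statement conditional, and asks for large-scale studies. Much of that stands, and it limits how serious the point is. It does not close the gap. The call for larger studies concerns evidence of efficacy, and the Discussion's condition is only that distinctive characteristics are found. Once it is met, no testing step precedes use as entry criteria.

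A second defence is that losing some responders is the ordinary price of enrichment. At 10/10 with a midpoint cut-off, the criterion keeps 68% of responders and admits 32% of nonresponders, so the responder share rises from 50% to 68/(68 + 32) = 68%. That is fair. But whether the trade is worthwhile can be judged only if the error rates are reported, and a t-test does not report them.

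A third defence is that some indicators are not continuous. Lesion location is categorical, and the Discussion's example of patent tracts could be read as present or absent. This stands: the AUC figures apply to continuous indicators only.

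A reader might infer that a marker chosen this way would turn away about a third of responders. The documents do not support that as a prediction. It needs a midpoint cut-off, a normal indicator, equal SDs and an equal split, none of which the protocol gives. With other cut-offs the loss could be 10% or over 60%. Nor does the t-test lack an error rate altogether: it has a type I error, and what it lacks is a classification error rate. A reader might also take the Discussion to say that the result would settle that stimulation suits only a few patients. It says only that this may be so.

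**Conclusion.** The point holds as a mismatch between the stated analysis and the stated use. Following the plan exactly would show which indicators differ in mean between responders and nonresponders. It would not show that any of them can select patients. A just-significant continuous indicator at N = 20 has an AUC of about 0.75 at 10/10, with an interval from little better than chance to near-perfect. A midpoint cut-off misclassifies about 25% to 32% on each side, and moving the cut-off exchanges one error for the other. These sizes rest on the assumed significance level, normality, equal SDs, the assumed splits and the observed difference being the true one.

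Because responders are pooled over the active and sham arms, even a well-separating indicator would show association with improvement, and not specifically with response to tDCS.

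**What to change.** - In Statistical and data analyses, report for each continuous indicator the AUC for responder status with its 95% CI, alongside the t-test. For lesion location, give a cross-tabulation by responder status.
- State there that these results are descriptive and pooled over both arms, so they describe association with improvement and not response to tDCS as such.
- In Sample size estimation and in the Discussion, replace the statements that markers serve as entry criteria with wording that they *are candidates to be tested as entry criteria*.

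Sensitivity and specificity by leave-one-out are not asked for. With 20 patients and no defined cut-off they would settle little.

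The cost is a small amount of extra analysis of data already being collected and two changes of wording. The downside is that the intervals will be wide and the claim more modest.

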### Objectives and hypotheses

In line with our rationale, the objectives of the present pilot clinical study are to: 1) examine the safety, feasibility and effectiveness of CIMT paired with tDCS targeting PMC, versus CIMT delivered alone in alleviating impairments of the paretic hand in patients with chronic stroke; and 2) assess neural markers associated with response to paired paradigm versus CIMT alone.

We hypothesize that the paired approach involving stimulation of PMC in the stroke-affected hemisphere will be more effective than CIMT in improving hand function in chronic stroke. The paired approach will facilitate the individual’s specific neural substrates of recovery and will be safe to employ throughout the length of the study.

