#### Structural neuroimaging

Predictors of response: diffusion tensor imaging defines the structural patency of white matter tracts
[55]. Using this method, we evaluate the integrity of corticospinal tracts, which are considered most critical to dexterity
[56]. We anticipate that PMC-based tracts will be more predictive of recovery with tDCS than those emerging from M1.

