### Interventions

#### CIMT

Once patients are randomly assigned to respective groups, patient-specific rehabilitation is delivered under supervision of the study principal investigator and physical therapist (EP) in an outpatient setting at the Cleveland Clinic main campus. All patients receive CIMT for 30 minutes, twice a day, 3 days a week for 5 weeks. It includes massed (intensive) functional exercises for the paretic upper limb guided by the principle of shaping
[47], which involves a graded, regimented, feedback-driven approach to achieving impairment- and patient-specific goals. Tasks focus upon transfer to real-world activities, including activities like grooming, making a telephone call, et cetera. The protocol of CIMT discussed here differs slightly from the modified version of the program that is generally employed
[46]. Instead of one 30-minute session, we deliver two 30-minute sessions; rather than 10 weeks, we deliver CIMT for 5 weeks, at the same frequency, that is, three times a week. We have incorporated this frequency and length to improve compliance, as patients are required to visit the outpatient clinic 15 times over 5 weeks rather than 30 times over 10 weeks. Patients’ use of the non-paretic upper limb is restrained by placing it in a mitt, which they are asked to maintain for 2 hrs every weekday during peak times of activity, instead of 5 hrs.

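### The responder comparison has no arm term, so it cannot tell a marker of response to tDCS from a general marker of recovery on CIMT

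*Protocol article*

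**What the plan says.** All places are in the protocol article.

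- **Objectives and hypotheses.** The second objective is to "assess neural markers associated with response to paired paradigm versus CIMT alone".
- **Structural neuroimaging.** A hypothesis specific to stimulation is added: "We anticipate that PMC-based tracts will be more predictive of recovery with tDCS than those emerging from M1".
- **Study design and CIMT.** "Twenty patients are being randomly assigned to PMC tDCS plus CIMT or sham tDCS plus CIMT groups", and "All patients receive CIMT for 30 minutes, twice a day, 3 days a week for 5 weeks".
- **Statistical and data analyses.** "Patients who achieve ≥3.5 gain in the UEFM score" after 5 weeks are responders. Two analyses use this class. The first is a chi-square: "We will investigate whether the proportion of responders versus nonresponders includes a greater majority of patients from the tDCS group". The second, which the text presents as the more important, is that "we will compare clinical, pathologic and neural indicators between responders and nonresponders" by independent-samples t-test. The listed indicators are baseline UEFM, lesion location, and corticospinal function (TMS) and integrity (diffusion tensor imaging).
- **Same section.** Possibly inadequate power is the reason given for using this method instead of predicting change in UEFM.
- **Discussion.** If responsive patients prove distinctive, "then these would serve as entry criteria for the future". Sample size estimation also foresees markers that could be used as entry criteria.

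**The concern.** Objective 2 and the premotor-tract hypothesis ask whether a marker relates to gain differently with tDCS than without it. The marker comparison sorts patients by gain alone. A sham patient who improves on CIMT counts as a responder just as a tDCS patient does, so a marker that predicts recovery equally well in both arms will separate the two classes.

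What is at stake is the label put on a positive result. If a general prognostic marker is reported as a marker of response to tDCS and then used to select patients for a stimulation trial, that trial would enrol patients who recover well anyway, with no enrichment for benefit from stimulation.

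**Working it through.** **1. Is the comparison pooled?** The text does not say so in words. The chi-square asks whether responders come more from the tDCS group, which makes sense only if responders can come from either arm. The next sentence uses the same two classes. No arm term, interaction or within-arm comparison is stated. Pooling is therefore an inference, but the natural one.

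**2. What does each analysis target?** Write

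gain = μ + τ·arm + b·marker + c·arm·marker + error, with arm = 0 for sham and 1 for tDCS.

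The marker slope is b on sham and b + c on tDCS. With equal arms, a comparison that ignores arm reflects roughly the average slope, [b + (b + c)]/2 = b + c/2. Objective 2 concerns c. So b alone can produce a positive result when c = 0. A tDCS-specific marker (b = 0) appears at about half its slope, and opposite slopes (b = −c/2) cancel.

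**3. How large is this?** The plan gives no figure for the marker analysis to reproduce; its power figures concern UEFM.

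- From the document: 10 patients per arm, responder cut-off 3.5, significance level 0.05.
- Assumed: two-sided tests, μ = 3.5, gain SD 4 in the sham arm, marker standardised to SD 1, and the values of τ, b and c.
- A prognostic correlation r gives b = 4r and error SD √(16 − b²). For r = 0.6, b = 2.4 and the error SD is √(16 − 5.76) = 3.2.
- 4,000 simulated trials per row; simulation standard error at most √(0.25/4000) = 0.8 percentage points.

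| Assumed truth | b | c | τ | Pooled t-test p<0.05 | Interaction p<0.05 |
|---|---|---|---|---|---|
| No association | 0 | 0 | 0 | 6% | 5% |
| Prognostic only, r = 0.4 | 1.6 | 0 | 0 | 29% | 5% |
| Prognostic only, r = 0.6 | 2.4 | 0 | 0 | 61% | 5% |
| Prognostic only, r = 0.6 | 2.4 | 0 | 3 | 51% | 5% |
| Prognostic only, r = 0.8 | 3.2 | 0 | 0 | 95% | 6% |
| tDCS-specific, 0.6 SD | 0 | 2.4 | 0 | 13% | 21% |
| tDCS-specific, 0.6 SD | 0 | 2.4 | 3 | 11% | 20% |
| tDCS-specific, 1 SD | 0 | 4 | 3 | 18% | 46% |
| Opposite slopes, ∓0.5 SD | −2 | 4 | 0 | 4% | 58% |

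Repeat simulations gave 29%, 62% and 93–94% for the three correlations with τ = 0, and 18–22% (pooled) against 47% (interaction) for the 1 SD tDCS-specific marker.

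**4. How to read the table.** The interaction's rate of about 5% in the prognostic rows is its nominal level under a null that was built in; it is not evidence in itself. The pooled rates in those rows are power to detect a real association with recovery. They become errors only if the result is called a marker of response to tDCS. Running the t-test in the tDCS arm alone does not cure this: at r = 0.6 with τ = 0 it is significant in 30% of trials for a purely prognostic marker. The contrast between arms is what is needed.

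**The case against.** **The study is a pilot and admits a compromise.** The article says an ideal method would predict change in UEFM, that power may be too low for it, and that an alternative is used. It calls the study exploratory and defers to larger trials. This bears on severity. It does not settle the point, because the article never says that the alternative drops the contrast between arms. Nor does low power favour the pooled test here: for tDCS-specific markers the interaction was significant more often. It is still weak, at about 20–47%, and would not reliably settle Objective 2 either.

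**The full plan may contain more.** The article is condensed, and within-arm summaries may exist elsewhere. But the classes and the test are stated, so this is a stated choice and not an omission.

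**Stronger readings that the documents do not support:**

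- A reader might infer that Objective 2 goes wholly unanswered. The same section compares the arms on change in inter-hemispheric balance, functional connectivity, transcallosal inhibition and corticospinal conduction. That analysis bears on how tDCS acts and stands. The Abstract also describes the aim as telling response from non-response, which the t-test does address.
- A reader might infer that the pooled test carries no information on benefit from tDCS. It can detect a tDCS-specific marker; it cannot tell one from a prognostic marker.
- A reader might infer that the markers will become entry criteria regardless. The Discussion makes this conditional on responsive patients proving distinctive.
- Chance baseline imbalance between arms could also surface as a marker if responders were mostly tDCS patients. That is not established, and its size was not calculated.

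**Conclusion.** The point holds for the markers-of-response part of Objective 2, the premotor-tract hypothesis and the entry-criteria use. A positive result from the planned comparison is ambiguous between prognosis on CIMT and response to tDCS.

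Under the assumed inputs, a purely prognostic marker is flagged in about 29–95% of trials for correlations of 0.4–0.8. A purely tDCS-specific marker is found in about 11–22%, against 20–47% for the interaction. These percentages depend on the assumed mean, SD and marker effects, none of which the article gives. The ambiguity itself does not depend on them; it follows from the missing arm term, given that the comparison is pooled.

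This should be fixed but is not critical. The aim is exploratory, and safety, feasibility and the primary UEFM analysis are unaffected.

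**What to change.** - **Continuous baseline markers.** For each one listed, add an exploratory model of UEFM change (or post-test UEFM adjusted for baseline) on arm, marker and marker × arm. Report the interaction estimate and the slope within each arm, all with 95% CIs.
- **Lesion location.** As a categorical variable it does not fit that template. Give responder status or mean gain by category within each arm.
- **Baseline UEFM.** It would be both marker and adjustment covariate, so use its own interaction with arm.
- **Responder comparison.** Keep it, state that it pools the arms, and label it as prognostic for recovery. Do not call its results markers of response to tDCS, and do not base entry criteria for stimulation trials on it alone.

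The cost is analysis and wording only; no new data are needed. The downside is that interaction intervals at n = 20 will be wide, so the results can only generate hypotheses and should be presented that way.

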### Participants and recruitment

We are enrolling patients with chronic stroke with mild-to-moderate impairments in upper limb function
[46,47], who fulfill the following prerequisites:

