### Inclusion and exclusion criteria

The inclusion criteria are: age ≥21 years; chronic phase of recovery (>6 months) after first-ever stroke up to 20 years post-stroke; ability to extend fingers or thumb or wrist ≥10° and chief complaint of inadequate ability to use the paretic hand compared to its use prior to a single (ischemic or hemorrhagic) stroke.

The exclusionary criteria relate to contraindications of cortical stimulation
[48,49] and imaging
[36,37]. These include: cardiac pacemaker; metallic implant in the head; seizure disorder; medication-resistant epilepsy in a first-degree relative; use of any neuro- or psycho-active medications as published in recommendations
[48]; history of fainting spells of undetermined etiology; pregnancy; implanted pumps/stimulators/shunts; any other neurological condition affecting sensorimotor systems, such as brain tumor, dementia, or substance abuse; severe cognitive deficits (mini-mental state exam score
[50] <18); ongoing/recent (within 2 months) rehabilitation for upper limb.

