### Study assessments

Following confirmation of eligibility, the pretest is scheduled over 2 days, and involves evaluation of upper limb function and neural markers of change. Post-test, following 5 weeks of the assigned intervention, is similar to the pretest.

Outcomes of hand function: the detailed timeline is presented in Figure 
1. Our primary outcome of hand function is the upper extremity Fugl-Meyer (UEFM) assessment, which measures impairments of the upper limb/hand
[51]. It is commonly used in studies pairing cortical stimulation with rehabilitation
[8-10]. It includes 33 items that provide a gross indication of overall functional status of an individual. It is rated on an ordinal scale (0 to 2, maximum score 66) by an investigator
[51].

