### Statistical and data analyses

Feasibility: analysis of feasibility includes investigating the rigor of experimental blinding and determining compliance with the 5-week outpatient rehabilitation program. A chi-square analysis will determine whether patients in one group versus another estimate their group assignment correctly. Investigators also complete a similar questionnaire at the end of the study. While patient responses will indicate the rigor of the blinding procedures, responses from investigators will ensure investigator equipoise, preventing observer bias. Attrition or missing data will be analyzed using a strategy known as multiple imputations
[65], where each missing value is replaced with a set of plausible values that represent the uncertainty about the true value. The multiple imputed data sets are analyzed using standard procedures used for complete datasets and by combining results from these analyses. The method of multiple imputations does not attempt to estimate each missing value through simulated values, but rather represents a random sample of missing values. This process results in valid statistical inferences that properly reflect the uncertainty due to missing values.

Safety: the incidence of adverse events in each group will be computed as a proportion of individuals in each group who experienced side effects. We will be using the Fisher exact test to contrast the incidence of side effects between both groups.

Efficacy and markers of recovery: our primary endpoint of efficacy is the UEFM. Secondary outcomes include nine-hole peg test, Action Research arm test, motor activity log, finger abduction strength and the modified Ashworth scale of spasticity. A general linear mixed-model approach will be followed to analyze functional outcomes across three levels of time (pre, post, and follow-up). Significant two-way interaction, whenever present, will be explored using the Tukey honestly significant difference (HSD) test. Non-parametric tests will be used if the distribution is not normal.

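### The responder comparison gives a t-test to stroke location, a three-class label, and its t-test of baseline UEFM is biased towards responders starting lower

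*Protocol article*

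**What the plan says.** All of this is in the protocol article.

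- **Responder definition** (Statistical and data analyses): "Patients who achieve ≥3.5 gain in the UEFM score" after 5 weeks are responders.
- **Test** (same section): "we will compare clinical, pathologic and neural indicators between responders and nonresponders (independent samples *t*-test". No other test is named for this comparison.
- **Indicators** (the next sentence): "These will include: baseline UEFM, location of disease (Oxford Stroke classification: total anterior circulation or partial anterior circulation or lacunar strokes", followed by corticospinal tract function (TMS) and integrity (diffusion tensor imaging).
- **Scale** (Study assessments): 33 items; "It is rated on an ordinal scale (0 to 2, maximum score 66) by an investigator".
- **Who is enrolled**: "mild-to-moderate impairments in upper limb function" (Participants and recruitment). The functional entry criterion is a minimum, "ability to extend fingers or thumb or wrist ≥10" degrees, together with a complaint of inadequate use of the hand (Inclusion and exclusion criteria). No upper UEFM limit is given.
- **Fallback** (Statistical and data analyses): "Non-parametric tests will be used if the distribution is not normal". This closes the paragraph on the mixed model for functional outcomes.
- **Size** (Study design): "Twenty patients are being randomly assigned to PMC tDCS plus CIMT or sham tDCS plus CIMT groups".

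**The concern.** There are two separate faults in one short list.

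**Location.** A t-test compares means, and a label with three classes has no mean. The analyst must first number the classes, and the p-value then reflects that choice. The chi-square test in the same paragraph concerns responder status by treatment arm, so it does not cover location.

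**Baseline UEFM.** The grouping variable is built from post-test minus baseline, and baseline is then compared between the groups so formed. A baseline score that is low by chance raises the apparent gain and the chance of being called a responder. The ceiling works in the same direction, because a patient who starts near 66 has no room to gain. Both push the comparison towards lower baselines among responders even when true gain has nothing to do with starting level.

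At stake is the reading of two of the four listed indicators. The article calls this comparison the more important use of the responder split, and its Discussion says that distinctive features of responders would become entry criteria for later trials.

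**Working it through.** The article gives no error rate, power or sample size for the responder comparison, so there is no figure of its own to reproduce.

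**1. Location: dependence on coding.** Take an illustrative split of 20 patients, in the order total anterior / partial anterior / lacunar: responders 1/4/5, nonresponders 4/4/2.

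With codes 1, 2, 3:
- Responder mean = (1 + 8 + 15)/10 = 2.4; nonresponder mean = (4 + 8 + 6)/10 = 1.8.
- Variances = (62 − 57.6)/9 = 0.489 and (38 − 32.4)/9 = 0.622.
- Standard error = √[(0.489 + 0.622)/10] = 0.333.
- t = 0.6/0.333 = 1.80 on 18 df.

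| Codes (total / partial / lacunar) | t | p |
|---|---|---|
| 1 / 2 / 3 | 1.80 | 0.089 |
| 1 / 3 / 2 | 0.82 | 0.42 |
| 2 / 1 / 3 | 0.75 | 0.46 |

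The other three codings mirror these. The Fisher-Freeman-Halton exact test on the same 3x2 table gives p = 0.29 under any coding.

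**2. Ceiling.** UEFM totals are whole numbers, so a gain of at least 3.5 means at least 4 points. From a baseline b the largest gain is 66 − b. At b = 62 this is 4, so response is possible. At b = 63 it is 3, so it is not. The ceiling therefore blocks response only at baselines of 63 to 66.

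**3. Size of the baseline bias.** The inputs below are assumptions, because the article gives none.
- True baseline is normal with the mean and SD shown.
- True gain has mean 4 and SD 3 and is independent of true baseline.
- Measurement error is independent at pretest and post-test, with the SD shown.
- Scores are rounded and limited to 0–66.
- n = 20, two-sided α = 0.05, 10,000 runs per row.

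Since gain is unrelated to baseline, a fair test would reject in 5% of trials.

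| Baseline mean (SD) | Error SD | Patients at ≥63 | Rejects, all patients | Rejects, ≥63 left out |
|---|---|---|---|---|
| 35 (10) | 0 | 0.3% | 5.3% | 5.2% |
| 35 (10) | 2.5 | 0.4% | 7.3% | 7.1% |
| 40 (10) | 2.5 | 1.5% | 8.9% | 7.4% |
| 45 (10) | 2.5 | 4.4% | 12.0% | 7.0% |
| 50 (10) | 3.5 | 11.9% | 25.8% | 8.1% |
| 52 (10) | 2.5 | 15.4% | 26.1% | 6.0% |
| 55 (12) | 2.5 | 26.9% | 42.0% | 5.6% |

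From mean 45 upwards, 96 to 100% of the false positives among all patients have responders lower.

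A second set, with gain SD 4, shows how far the answer moves with the inputs:
- Mean 50, SD 8: 7.8% with no error, 14.6% with error SD 2.5, 24.6% with error SD 4.
- Mean 55, SD 8: 20.5%, 31.9% and 42.6% for the same error SDs.
- Mean 35, SD 10, error SD 4: 11.5%, from shared error with almost no ceiling.

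The last column of the table separates the two causes. Without the patients who cannot respond, rejection falls to about 5 to 8%, so the large values come mainly from the ceiling and the remainder from shared measurement error.

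**The case against.** The strongest reply is on size. Without a baseline mean, SD or measurement error, the bias may be slight: if patients average 35 with little measurement error, the test is close to nominal. The 26% and 42% figures need roughly 15% and 27% of patients (3 and 5 of 20) within three points of a perfect score. That is a lot in a trial whose patients must complain of inadequate hand use. This stands, and the size can only be given as a range.

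A second reply is that the three classes could be read as ordered. The Discussion contrasts subcortical lesions with massive total anterior infarcts. But the analysis section states no order, and a t-test would also need equal spacing. The non-parametric fallback does not help: it is triggered by non-normality, is written for the functional outcomes, and would still need an order.

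Third, the study is an exploratory pilot, and the article offers the responder split as a substitute because predictor modelling may lack power. That limits the weight of the point, but low power is a different matter from a test that does not fit its variable.

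A reader might go further than the documents allow in three ways:
- **That baseline UEFM cannot be tested at all.** It is numeric and the t-test can be computed; the fault is bias.
- **That the ceiling pushes intact tracts into the nonresponder group.** This needs a correlation between tract integrity and UEFM that the article does not give, and it was not computed.
- **That these two indicators are the planned entry criteria.** The article speaks of neural markers, with intact, functioning white matter tracts as its example, and names neither baseline UEFM nor location.

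**Conclusion.** The point holds in two parts of different strength.

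For location, the test is wrong as written. This follows from the text alone and needs no assumption.

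For baseline UEFM, the direction of the bias is certain and its size is not. Assuming n = 20 and true gain unrelated to baseline, the false-positive rate runs from about 5 to 9% at a baseline mean of 35 to 40, through 11 to 12% at 45, to 25 to 42% at 50 to 55 where 12 to 27% of patients start at 63 or above. At the same means with a narrower spread and little measurement error it is lower, 7.8% at the least. A significant result with responders lower at baseline could not be taken as evidence of a marker.

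The mixed model for the primary UEFM outcome is not affected.

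**What to change.** Change the wording of the responder analysis in three places:

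1. Test stroke location with a Fisher-Freeman-Halton exact test on the 3x2 table, and keep the t-test for the continuous markers.
2. Report baseline UEFM by responder status descriptively, without presenting it as a test of a marker.
3. Report how many patients have a baseline UEFM of 63 or more, and repeat the responder comparisons without them, because they cannot meet the definition.

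The cost is one p-value fewer and slightly fewer patients in that sensitivity comparison. Recruitment, treatment and data collection do not change. More elaborate remedies are not needed at n = 20. Putting location into a continuous UEFM model, for example, would return to the predictor approach that the article set aside for lack of power.
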